### Data Collection and Management

The information will be handled confidentially to prevent participant names or other directly identifiable information from appearing in any report, publication, or other disclosure of results. Data (eg, name, age, length of illness) are collected and stored in separate folders. The investigator will enter the pseudonymous data into a database for statistical analysis.

Essential documents shall be archived in such a way as to ensure that they are readily available, on request, to the competent authorities.

The collected data of the PC4L components are only made available in a pseudonymized form in the secure cloud “Amazon Web Services,” which is located within Europe [32]. The patient will therefore be assigned a code to ensure the pseudonymity of his/her data. The data on the cloud are only accessible to the project partners, with whom a data processing agreement was made.

The data processing agreement was stipulated as an agreement between the data controller (partner 1, ie, clinical partners collecting the data) and a data processor (partner 2, ie, partner responsible for data analysis) within the consortium, with the purpose of regulating the processing of any personal data collected. In the context of joint controllers, partner 1 is responsible for the processing of personal data in a conventional form from participants (health data and medical data set derived from patients involved in the user requirements phase and in the pilots, data from caregivers, professionals, and other stakeholders). Partner 2 is—within the framework of joint controllers—responsible for the processing of personal data in device data and annotations (social and medical data set/audiovisual).

The data obtained will be used only for the purposes of the research and not for other purposes. The results of the research will be shared more widely, for example, through publications and conferences, but no personal information will be displayed. The processing, communication, and transfer of personal data will be carried out in accordance with the provisions of Regulation (EU) 2016/679 [33] and Law 3/2018 [34], of 5 December, on the Protection of Personal Data and the Guarantee of Digital Rights. In accordance with the legislation, the participant may exercise his/her rights of cancellation, opposition, portability, limitation, access, and rectification by contacting the professional who informed the participant about the project. Likewise, the consortium adheres to the principles of the General Data Protection Regulation (GDPR; legality, equity and transparency; purpose limitation; minimization of data; accuracy; storage limitation; integrity and confidentiality; and responsibility).

Any inaccuracy regarding the functioning of the system will be promptly reported to the technical partners of the project who will intervene in correcting them. The interruption of operation of 1 or more components of the PC4L system will not have any kind of feedback/effect on the participant.

### Ethics Approvals

#### Study Approval

The study protocol was reviewed and approved by the local ethical committees in Germany [number 2022-29-MB-FA4, Ethical committee of Westfälische Wilhelms-Universität (WWU), Münster], Italy (number 734-2022bis, Comitato Etico Milano Area 2), Portugal (number 6-2022 R, CNS Ethic Committee), Romania (numbers 7/19.07.2022, Comisia de Etică a Cercetării din Spitalul Colentina and 36432, Comitetul local de etică SUUB/ Spitalul Universitar de Urgență București), and Spain (number 22/392-E, Ethical committee of Hospital Clinico San Carlos – Salud Madrid). The institutional review board of all centers approved the study and will receive study reports during mid-study and at the end of the study, and will monitor the study implementation and data collection. Any deviations from the protocol will be promptly notified to the ethics committees and applied only after its approval.

The randomized controlled trial has been registered at ClinicalTrials.gov (identifier NCT05538455).

The study is conducted in accordance with the principles of the Declaration of Helsinki.

The results of this study will be disseminated through peer-reviewed journals and national and international academic conferences only by the professionals directly involved in the clinical trial.

#### Patient’s Informed Consent

After the study had been fully explained to the patient, written informed consent was obtained prior to any study-related proceedings. The method of obtaining and documenting the informed consent and the contents of the consent comply with ICH-GCP (International Conference on Harmonisation good clinical practice), all applicable regulatory requirements, and legal requirements.

In case the patient is unable to read or sign, a legal guardian is allowed to sign the informed consent, only after confirming that the study has been comprehensively explained to the patient by the research team.

#### Security and Adverse Event Reporting

Any adverse event (serious or nonserious) and any other abnormal clinical, personal, social finding will be recorded in the patient’s case report form. For all adverse events, sufficient information will be pursued to permit the following:

a determination of a temporal relationship;an adequate determination of the outcome of the event (ie, whether the event should be classified as a serious adverse event); andan assessment of the casual relationship between the adverse event and the study requirements.

An abnormal result finding will be classified as an adverse event if 1 or more of the following criteria are met:

the result finding leads to a discontinuation of patient participation in the research study andthe result finding is considered an adverse event by the researcher.

### Withdrawal of Participants

Participation in this study is voluntary. Patients may withdraw from the study at any time, without giving reasons and without disadvantage in terms of the quality of care they would receive if they did not participate. After the withdrawal, no further data will be collected or taken into consideration for statistical purposes.

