### Aims

This study represents the third, and last, phase (pilot 3) of large-scale pilots aiming to gradually co-design and iteratively test the PC4L integrated platform and modules.

While pilot phases 1 and 2 focused on technical feasibility and patients’ satisfaction, this protocol focuses on the following objectives:

To assess the impact of using the PC4L platform on patients’ quality of lifeTo compare the metrics generated by the PC4L platform in real-life conditions with the clinical outcome measuresTo evaluate the feasibility and safety of measuring disease progression and patient health status through the global functioning of the PC4L systemTo assess and compare the feasibility and usability of 2 different versions of the PC4L system (fully equipped version vs cloud-based solution)To increase patients’ safety and empowerment

As the primary outcome, the study will provide:

The difference in quality of life between groups (experimental vs control group), measured by the EQ-5D-3L scale at the end of the study

The following secondary outcomes will also be acquired:

The correlation coefficient of the PC4L platform metrics (eg, steps and physical activity levels, sleep, number of falls, cognitive scores) with the clinical outcome measures (eg, motor clinical evaluation, sleep questionnaire, Falls Efficacy Scale-International [FES-I], cognitive evaluations) measured at baseline, end of the study, and the values of change from baselineSystem usability assessment, measured through the System Usability Scale (SUS), at the end of the studyUsers’ satisfaction with the PC4L system, measured through a 5-point Likert Scale, the mHealth User Satisfaction Questionnaire, and the participants’ answers to open questions, at the end of the studyChanges in patients’ satisfaction and empowerment, measured by the Patient Assessment of Chronic Illness Care (PACIC) and the Short Assessment of Patient Satisfaction (SAPS) scales, respectively, at baseline and at the end of the studyChange in patients’ use of medical resources (number of admissions and number of days spent in health institutions) in the last month, measured at baseline and at the end of the study

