### Recruitment

Patients with PD and other parkinsonian syndromes, AD, or ODs were invited to participate from the clinical centers involved in the study. Each participant organization was assigned to recruit a number of participants related to their skills, experience, number of researchers involved, and access to users (Table 2).

**Table 2 table2:** Distribution of participants per clinical center and scenario.

Scenario/clinical center	Rehabilitation (n=204), n	Day care (n=82), n	Home (n=272), n	Total (N=558), n
APM^a^	80	N/A^b^	26	106
CCP^c^	63	N/A	62	125
CNS^d^	46	N/A	86	132
UHB^e^	15	N/A	15	30
UMF^f^	N/A	30	30	60
WBW^g^	N/A	52	53	105

^a^APM: Asociacion Parkinson Madrid.

^b^N/A: not applicable.

^c^CCP: Casa di Cura del Policlinico.

^d^CNS: Campus Neurológico Sénior.

^e^UHB: University and Emergency Hospital of Bucharest.

^f^UMF: University of Medicine and Pharmacy.

^g^WBW: Wohlfahrtswerk für Baden-Württemberg.

To reach the planned number of recruits, many strategies were implemented: participants were contacted through online webinars; through brochures placed in specific centers such as pharmacies, leisure centers, and medical offices; and through patients’ associations. Further, regular updates were posted via online newsletters on different websites, such as the PC4L website and end users organizations’ websites. In addition, information about the PC4L pilot 3 study was shared during national and international conferences. Recruitment was also promoted in a collaborative way thanks to partners from other European projects. Finally, participants were recruited in person when accessing the medical facilities and via phone contact or emails after searching local databases.

Patients who discontinue the study participation because of medical conditions (ie, infections, falls, medical emergencies) or unwilling to participate any longer for other reasons (ie, difficulty with technology, loss of interest) will be considered dropouts.

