#### Intervention Group

The patients recruited and assigned to the experimental group received specific instruction in using the project platform, but without any specific program concerning the activities.

Specifically, patients, after the baseline assessment, received the instrumental setup and indications on its functionalities. Patients were instructed about the use of the Fitbit, the PC4L app, and the cognitive games on a tablet or computer. Patients were also provided with manuals.

Specifically, according to the study approach detailed by Biehl et al [9], the patients were instructed to complete the following questionnaires in the app during the first week and during the last week of the study period: the 10-item Eating Assessment Tool (EAT10) [13] for evaluation of dysphagia; the Edmonton Symptom Assessment System (ESAS) [14] and the Patient Global Impression (PGI)—Severity [15] for evaluation of symptoms; and the International Physical Activity Questionnaire (IPAQ) [16] for evaluation of physical activity. In addition, during the last week of using the app, patients were requested to complete the SUS [17], via the app, for evaluation of usability.

The platform was installed in each scenario with the assistance of the project research staff (ie, bioengineers).

A total of 2 versions of PC4L systems were installed: while the cloud-based system (which only required a smartphone and a wearable sensor) was used in all scenarios, a fully equipped version was implemented only in the rehabilitation scenario.

The patients received the same directions in all 3 scenarios.

At the end of the study period, patients performed end-of-study evaluations and returned the instrumental setup.

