#### Usability and Satisfaction Assessment

At the end of the experimental period, patients allocated to the experimental group performed the usability evaluation of the PC4L platform solution by means of the SUS [17], Global Satisfaction and mHealth User Satisfaction questionnaires, adverse events reporting, and end-of-study open questions.

The SUS is used to measure how easy or difficult the proposed system is to use. We will compare the usability of 2 different versions of the PC4L system (fully equipped and cloud-based solutions). The overall SUS score will be calculated and assessed consistently with the literature: a score of 100 corresponds to the best imaginable usability, while acceptable usability is defined by an SUS score above 68 points [17,25].

The Global Satisfaction Questionnaire is used to assess the overall level of satisfaction or dissatisfaction with the platform experience.

The mHealth User Satisfaction questionnaire is used to measure user satisfaction and usability of the recommendation component of the solution [26].

As a completion of end-of-study assessment, an adverse events report and end-of-study open questions of preferred and less preferred aspects of the platform, as well as suggestions for improvements, will be collected for each user.

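### Stopping PC4L is not separated from leaving the study, and the SUS is collected through the app: usability is likely overstated, and the EQ-5D-3L comparison is open to bias of uncertain direction

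*Protocol article*

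**What the plan says.** The Recruitment section defines dropouts by two kinds of reason. The first is medical: "Patients who discontinue the study participation because of medical conditions (ie, infections, falls, medical emergencies) or unwilling to participate any longer for other reasons". The second is given in the bracket that follows: "ie, difficulty with technology, loss of interest) will be considered dropouts".

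The section on Withdrawal of Participants then states: "After the withdrawal, no further data will be collected or taken into consideration for statistical purposes". No sentence distinguishes a patient who stops using PC4L but would still be assessed from one who refuses further assessment.

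The primary outcome under Aims is "The difference in quality of life between groups (experimental vs control group), measured by the EQ-5D-3L scale at the end of the study". Study Assessments makes the end-of-study evaluation an in-person visit, at 3 months or at discharge from rehabilitation.

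On the SUS, the Intervention Group section says that "during the last week of using the app, patients were requested to complete the SUS [17], via the app, for evaluation of usability". The Usability and Satisfaction Assessment section says of the final assessment that "patients allocated to the experimental group performed the usability evaluation of the PC4L platform solution by means of the SUS" and other questionnaires, without naming a way to reach those who had stopped. It sets the yardstick: "acceptable usability is defined by an SUS score above 68 points".

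**The concern.** Two of the listed reasons for dropping out are tied to what the trial measures. Falls and illness bear on quality of life; difficulty with the technology bears on usability. Control patients receive written recommendations and no system, so difficulty with the technology can in practice remove patients only from the PC4L arm. One route of loss is thus specific to an arm by design. If those patients would have fared differently from the ones who stayed, the groups compared at the end are no longer the groups that were randomised. An analysis plan cannot recover data that the protocol says will not be collected.

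For usability the difficulty is close to circular. The question whether the app can be used is put through the app, late in its use. Patients who could not manage it are the least likely to answer, yet the resulting mean is read against a fixed threshold. The planned SUS comparison of the fully equipped and cloud-based versions is exposed as well if the two versions lose users at different rates.

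**Working it through.** **The plan's own figure.** The Sample Size section gives 279 per group for a 6-point difference with 95% power and no allowance for dropouts. It gives no SD, so 279 cannot be reproduced. Solving backwards for a two-sided 5% test: SD = 6 × √(279/2) / (1.960 + 1.645) = 6 × 11.81 / 3.605 = 19.66. This implied SD is used below only to turn a shift into an error rate.

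**From rule to missing value.** A patient who leaves early is a dropout (Recruitment). Nothing further is collected after withdrawal (Withdrawal of Participants). The end value comes from an in-person visit (Study Assessments). The patient therefore has no end value, and the paired tests named under Statistical Analysis need one.

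**EQ-5D-3L.** Let p be the share lost in an arm and g the number of points by which the lost patients are worse than those who stay. Comparing only those who stay shifts the difference towards PC4L by

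shift = p(PC4L) × g(PC4L) − p(control) × g(control).

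All rates and gaps are assumptions, and so is reading the points as a 0–100 scale.

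| Loss and gap, PC4L | Loss and gap, control | Shift (points) |
|---|---|---|
| 20%, 20 | none | +4.0 |
| 20%, 10 | 5%, 10 | 2.0 − 0.5 = +1.5 |
| 10%, 10 | none | +1.0 |
| 5%, 6 | none | +0.3 |
| 15%, 10 | 15%, 10 | 1.5 − 1.5 = 0 |
| 15%, 10 | 10%, 20 | 1.5 − 2.0 = −0.5 |
| 15%, 0 | 10%, 10 | 0 − 1.0 = −1.0 |

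A shift of +1.5 is a quarter of the 6-point target (1.5/6). In a two-group comparison of end values with SD 19.66, 10% loss in the PC4L arm alone and a gap of 10 points would raise the two-sided type I error from 0.05 to about 0.09. The +4.0 row would raise it to about 0.62.

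The formula applies to end-of-study levels. In an analysis of change from baseline, g is the gap in change. If leavers were 10 points worse at both visits but would have changed as much as those who stayed, then g = 0 and the shift is 0.

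**SUS.** Let C be the mean of completers, L the mean that leavers would have given and q the share who stop. Then the all-user mean = (1 − q) × C + q × L, and the overstatement = q × (C − L). This is positive whenever L is below C. With C = 72 (assumed):

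| q | L = 35 | L = 45 | L = 55 |
|---|---|---|---|
| 10% | 68.3 | 69.3 | 70.3 |
| 20% | 64.6 | 66.6 | 68.6 |
| 30% | 60.9 | 63.9 | 66.9 |

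For L = 45 and q = 20%: 0.8 × 72 + 0.2 × 45 = 57.6 + 9.0 = 66.6. The all-user mean falls to 68 at q = (72 − 68)/(72 − 45) = 4/27 = 14.8%, about 41 of the 279 PC4L patients. Break-even is 4/37 = 10.8% for L = 35 and 4/17 = 23.5% for L = 55. Over q from 5% to 30%, C from 68 to 72 and L from 35 to 55, the overstatement runs from about 0.7 to 11.1 points.

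**The case against.** The strongest reply is that both passages speak of leaving the study. Neither says that a patient who puts the wristband away, or has a fall, but still consents will lose the end visit. Ending collection once consent is withdrawn is normal practice. This stands: the fault is that the boundary is not drawn, not that the article orders device-stoppers to be discarded.

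A reader might infer more: that both outcomes are biased towards PC4L, because PC4L completers are compared with nearly all controls. The documents do not support that for quality of life. Infections, falls, emergencies and loss of interest can occur in either arm, no loss rates are given, and nothing shows that controls are almost fully retained. As worked above, the shift can be zero or run against PC4L.

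On usability, the article also plans satisfaction questionnaires and open questions on less preferred aspects, none stated to be app-only, and it describes the evaluation as done by patients allocated to PC4L. It excludes patients whose severe cognitive decline would compromise device use, and it provides instruction and manuals. These measures may lower the number who stop. They do not give a route to the SUS for those who do, and the threshold of 68 applies to the SUS.

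Sensitivity analyses may sit in an analysis plan that is not shown, so their absence here is not the point. Keeping data gathered before withdrawal is also not contradicted, since the rule bars only further data. What the article does fix is the collection rule and the SUS channel.

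**Conclusion.** The concern holds in two parts of different strength.

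For the SUS it is well founded. Collected as the Intervention Group section describes, the mean comes from patients still able to use the app, and it is overstated whenever those who stopped would have rated the system lower. Under the illustrative values of 72 and 45, a pass among completers becomes a fail among all users once more than about 15% stop.

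For the EQ-5D-3L it is a risk, not a demonstrated bias. Loss is likely to differ by arm because one listed reason belongs in practice to the PC4L arm. A shift towards PC4L is possible, but its sign and size rest on loss rates and gaps that the article does not give and, in an analysis of change, on how leavers would have changed. The assumed scenarios span -1.0 to +4.0 points.

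This should be corrected because it touches the primary outcome and a secondary outcome with a stated threshold.

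**What to change.** 1. In Recruitment and in Withdrawal of Participants, separate stopping PC4L from withdrawing consent to assessment. Apply the rule against further data only to the latter, and seek the end-of-study EQ-5D-3L, by phone if needed, from every randomised patient who still consents.
2. Obtain the SUS on paper or by phone from every PC4L patient, including at the time of stopping.
3. Report loss by arm and reason, keep data collected before withdrawal, and add a sensitivity analysis that assumes worse outcomes for dropouts and counts technology dropouts as not reaching 68.

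The cost is one short extra contact for patients who stop, plus changes in wording; those who refuse contact stay missing. Timing limits the first two steps. Enrolment ended in February 2023 and participation lasts at most 3 months, so follow-up would have been due to end by about May 2023, before the article appeared in July 2023. Steps 1 and 2 may therefore be feasible only in part. Step 3 needs no new data collection and remains feasible.

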## Results

The recruitment began in September 2022, and enrollment ended in February 2023. Recruitment is now closed (April 2023). The results of this study are expected to be published during the summer 2023.

The results of this study will be presented at national and international patients’ organizations and to the public.

The study protocol is part of a project (grant agreement number 875221) approved and funded by the European Commission in the framework of Horizon 2020 action.

The results of pilot 3 will allow clarification of the usability of the final version of the PC4L system, its impact on patients’ and caregivers’ quality of life, empowerment, and use of medical resources. It would also provide information on the support of the system as a tool to facilitate the decision-making process.

At the time of the deployment of this study, as for the previous protocols, issues due to the COVID-19 pandemic in European countries were managed to avoid safety-related risks.

## Discussion

PC4L recognizes that today in health care an integrated care process should be adopted for harmonizing health models with social services from a holistic perspective [35]. Therefore, the project intends to develop and test a technology-based, integrated, scalable, and interactive care platform by involving patients with neurodegenerative diseases, such as PD and dementias. The principal aims of this project are to improve the quality of life of patients and to enable active living and better disease management. These aims will be achieved through large-scale assessments across Europe (in 5 countries and 6 end user organizations), with the final scope to validate the reliability of the overall system in a real-life context.

Eventually, the main advantage of the PC4L project is to propose a system that can be easily adapted to the reality of various chronic diseases, care institutions, and end user needs, thus benefiting all actors involved.

To assess the impact on quality of life and usability, we decided to adopt a randomized controlled trial model because it minimizes selection bias and allows reaching an adequate sample size to achieve power.

In the context of improved technologies and digitalization strategies, the use of wearable sensors and smartphone apps has the advantage of providing objective, longitudinal, and precise information about the status of the patients in their own home environment, as highlighted by Klucken et al [36], especially in cases of neurodegenerative diseases.

Based on the extensive literature on the benefit of physical activity in neurodegenerative diseases [37-46], we expect an improvement in quality of life. This is also facilitated by the early detection of signs and symptoms (eg, falls) through proactive monitoring.

Moreover, in terms of digital health, the inclusion of participants is a crucial part [47]. Based on our recent work, we considered that the ICT-integrated care platform should not promise functionalities that are too complex for too many users [11]. Instead, we focused on selection and restriction to fewer but essential aspects. Users and other stakeholders have in fact been involved in these decisions by being considered active actors from the early stages of the project. Notably, the clinical study here described is conducted in 3 different real-life scenarios, providing relevant information on the everyday life of the patients.

Regarding the home scenario, the primary advantage of implementing this scenario is the ability to monitor patients at home, measuring their general health condition, asking about their perceived state, and detecting their symptoms (eg, gait disturbances or falls). The acquisition of these data will enrich patients’ perception of their own condition and will allow the comparison between their insight and the clinical and instrumental data. Health professionals, from their perspective, can take advantage of all these data by adapting the prescribed therapy in a highly personalized manner. Thus, patient-doctor communication will be improved, facilitating patients’ engagement with their own health care process.

Central to the study is also the implementation of the PC4L solution in the rehabilitation centers, as such controlled environments involve patients in different kinds of activities, under the supervision of a multidisciplinary team. Here, patients perform personalized treatments in dedicated rooms, such as motor training and exercises connected to ADL, as well as cognitive exercises to improve memory and attention. The main advantages of PC4L in this scenario are (1) the possibility to provide objective information to professionals to study the evolution, treatment personalization, and rehabilitation suggestions; (2) to check the communication between professionals, patients, and caregivers, especially exercise recommendations based on the evolution of patient’s movement skills; and (3) to design a decision support tool taking into account the patient’s personal and health condition.

Finally, in the third scenario of day care centers, patients perform activities connected to ADL like at home, but under the supervision of professionals (day care center workers). Additionally, the participation of caregivers in this scenario can support the patients. The benefits are to check the communication between professionals and the caregiver, who does not live in the same house with the patient, and to monitor the patient’s evolution.

In this pilot study, as already reported by Espay et al [48], low digital skills could be a limitation to the appropriate use of the PC4L solution and, therefore, the correct monitoring of the participants. The consortium mitigated this risk by adopting simplified age-appropriate questionnaires and tools.

Another risk could be the completion of the recruitment of the patients: for this purpose, the consortium of PC4L has adopted several mitigation measures (described earlier).

Trying to provide a balance between an acceptable benefit-to-burden ratio and the delivery of reliable, clinically relevant insights, through mobile health (mHealth) technologies, as suggested by Espay et al [49], the main solution of PC4L includes the continuous use of the wristband for monitoring parameters such as steps and levels of physical activity, and the PC4L app, which includes easy but engaging functionalities.

The final goal of the PC4L project is to obtain a good coordinated care model between all involved actors. Future developments of such projects might dwell into the active involvement of caregivers and socio-health professionals and into the support of professionals in the decision-making process, to facilitate efficient communication between all stakeholders and ensure reliable and protected access to data within Europe [8].

